#### *8.7.8.2. Verbal autopsy visit*

All parents of children who die will be visited at home as soon as possible for a detailed verbal autopsy interview using standardized questionnaires that will be used to categorize the potential cause of death as probable, possibly, or not malaria related.

## **8.8. SAMPLE SIZE**

### *8.8.1. Trial*

#### *8.8.1.1. Sample size re-estimation*

Following recommendations from the DMEC and TSC, a blinded interim sample size re-estimation was conducted to take the lower than expected rate of loss to follow-up into account and the higher than expected pooled event rate of the composite primary endpoint (death or all-cause readmission) across both arms. This was favoured over an interim analysis, because the available funding did not allow and extension of the recruitment period, even if the results of any interim analysis would suggest this was required.

The revised sample size calculations were conducted in PASS (v15) software using a tests for the ratio of two Poisson rates. A total sample size of 1040 children (520 per arm) is required to detect a 25% reduction in the incidence of the composite primary outcome from 1,152 per 1000 child years (530 events per 1000 children during the 24 weeks from randomization at 2 weeks to the end of follow-up at 26 weeks) in the control arm to 864 per 1000 child years (398 per 1000 children over 24 weeks) in the intervention arm (power 80%,  $\alpha=0.05$ ), allowing for 10% loss to follow-up. The same

sample size would also provide 90% power to detect a 28.7% reduction in the primary endpoint from 1,152 to 822 events per 1000 children years.

#### 8.8.1.2. Original sample size estimation

Sample size calculations were conducted using EAST (v6.2) Software. The total sample size will be 2212 children (1106 per arm) across both countries pooled. A sample size of 1858 is required to allow detection of a 30% reduction in the mean incidence rate (incidence density) of the composite primary outcome (death or all-cause readmission) from 469 per 1000 child years (216 events per 1000 children during the 24 weeks from randomization at 2 weeks to the end of follow-up at 26 weeks) in the control arm to 328 per 1000 child years (151 per 1000 children over 24 weeks) in the intervention arm (power 90%,  $\alpha=0.05$ ). A single child can have multiple (repeated) primary events. 1865 children are required to allow for 1 interim analysis using the Lan-DeMets spending function with O'Brien-Fleming type boundaries to preserve the overall two-sided type I error rate for efficacy (see 9.5.1.2, page 49). To allow for 15.7% loss to follow-up a total of 2212 children will be conducted.

The impact estimate of 30% is based on the previous trial in Malawi where the protective efficacy (PE) with monthly AL was 30% (and 31% for death or admission for malaria or anaemia). The incidence rate of 469 per 1000 child years is the average incidence rate observed during the 2-26 weeks post-discharge period in the control arm in the previous trial in Malawi (536 per 1000 child years) and the rate in western Kenya in 2013 (402 per 1000 child years). The estimated rate of loss to follow of 15.7% is conservative and three times the rate observed in our previous studies that involved 6 months follow-up of children admitted for severe malaria or severe anaemia: this was 7.4% in the earlier IPTpd/PMC trial in Malawi across 4 hospitals, and 3.5% and 5.0% in two previous observational studies in Uganda. However the study will involve a total of 7 hospitals, only 3 of which are experienced research hospitals. We have therefore allowed for 15.7% loss to follow-up, which is the average of 10% in the 3 experienced sites and 20% in the remaining 4 sites.

#### 8.8.2. Cardiac monitoring study

A sample size of 26 children is required to achieve 90% power to detect a difference of 20.0 ms in QTc time between the mean QTc observed 4 to 6 hours after the 3rd dose of the first 3-day course of DP at 2 weeks and the last dose of the last 3-day course of DP at 10 weeks, assuming an estimated standard deviation of 31.0 (two-side alpha 0.05). The SD values are based on observations from previous studies in Uganda with monthly IPT with DP in children 6 to 24 month of age. To account for 20% loss to follow-up or missed ECGs, 33 children will be recruited. Because the study is placebo controlled 33 children will be recruited per arm; i.e. 66 in total.

## 8.9. RECRUITMENT STRATEGIES FOR ACHIEVING TARGET SAMPLE SIZE

The enrolment of the target sample size is scheduled to be completed in a 24-month period, requiring an average of 316 children per site (for 7 hospitals), or 158 per site per year. The study sites in each country will be chosen based on their potential to recruit at least 200 children, based on the number of cases receiving blood transfusion within the given age range. The presence of other studies that could potentially restrict the number eligible children will also be taken into consideration. Recruitment will be competitive between sites in each country to enhance the

chances of completion within 2 years. Recruitment will start in approximately 7 hospitals and can be expanded to approximately 10 hospitals if low recruitment rates are encountered. We have therefore included additional backup hospitals (see 8.3, 'Study settings', page 23).

## 8.10. ASSIGNMENT OF INTERVENTIONS AND BLINDING

### 8.10.1. Allocation

#### 8.10.1.1. Allocation sequence generation

Eligible children will be randomly assigned to either PMC or placebo group with a 1:1 allocation as per a computer generated randomisation schedule stratified by age group and site using permuted blocks of random sizes. The length of each block will be randomised and will not be disclosed to ensure blinding is fully maintained.

The randomisation schedule will be drawn-up in advance by the study statistician. Recruitment will be 'competitive' between the sites within a country (i.e. the number of subjects recruited at each site may differ depending on the respective rates of admission). To allow for this, 600 individual randomisation envelopes will be prepared for each site to ensure equal distribution across study arms within each site.

#### 8.10.1.2. Allocation concealment mechanism

The active PMC and placebo drugs for each participant will be pre-packed in opaque sealed envelopes containing 3 other envelopes (one for each PMC course) or a sealed box with three bottles. The envelopes or bottles containing active DP or placebo will look identical, and the appearance and consistency of the tablets will also be identical. Each envelop or box will be prepared with the sequential numbers, but not yet with the study subject number supplied. The preparation and packing of the study drugs will be performed by a dedicated pharmacist assistant who will remain unblinded during the study in order to package the blinded subject-specific study treatment, in accordance with the randomisation scheme. He/she will not be involved in any other component of the study. Because the master code and individual codes are kept in sealed envelopes in a central location off site (see section 8.10.2), neither the caretakers, study staff, nor investigators will be able to know the next study group assignment in the allocation sequence.

#### 8.10.1.3. Allocation implementation

The allocation will occur at 2 weeks post-discharge, during the first PMC treatment visit, just prior to the first dose of PMC. On the day of randomization for each child, the child's study identification number will be recorded against each envelope/box number by writing the study ID on the envelope or box prior to it being opened. Once the participant's study ID has been written on the envelope/box, the child will be considered randomized.

No subject will be randomised into the study more than once. If a subject number is allocated incorrectly, the subject number should not be reassigned and randomisation should continue with the next sequential number. The sponsor should be informed immediately and the investigator will be instructed on other appropriate procedures to be followed.

All enrolled subjects who subsequently do not meet eligibility requirements for randomisation at visit 4, 2 weeks later, will be considered screening failures and will not be randomized, with the exception of children that fulfil the criteria to delay randomisation as described in section 8.4.3, 'Eligibility criteria for randomisation into study (at 2 weeks)', page 27.

### 8.10.2. Blinding

Neither the caretakers, study staff, nor investigators will know which arm a child is in. Thus the treatment group may only be determined by comparing the child's study id to the blinded list of envelope/box numbers. The master code to randomisation code will be kept in a sealed envelope. Only the study pharmacist (on site), and the trial statistician and the DMEC statistician (both off-site) will have access to master-code until the study is completed or stopping rules are reached and unblinding is required. The randomisation scheme will also be available to the principal site investigator and the study safety monitor, but only as individual treatment code envelopes, indicating the treatment for each randomised subject. The international collaborators, clinical monitors, or other personnel from any Contract Research Organization (CRO) handling the data on behalf of the sponsor, will have no access to the randomisation scheme. The treatment allocations will be disclosed after the data is locked and a statistical analysis plan has been submitted to the DMEC.

All laboratory tests will be conducted by subject study number, date of birth and date of sample. Laboratory personnel will be unaware of the randomisation group of the subject. The study statistician conducting the interim analysis will remain blinded throughout the analysis.

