### 9.2. STATISTICAL METHODS

A detailed study statistical analytical plan for the final analysis, that will supersede the study protocol, will be drawn up during the course of the study before the unblinding of data at database lock.

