#### 16.3.3.2. Role DMEC

The DMEC consist of 3-4 members (including one or more clinicians and one statisticians, all with experience in clinical trials).

The DMEC shall assess the data regularly (before the annual TSC meeting) to review the data and the interim analysis. The assessment could be via email or other electronic medium annually prior to the TSC meeting. In the first year of recruitment more frequent assessment (bi-annually) is recommended for this trial with one face to face meeting at least once during the trial.

The members should be the only personnel to see the results separated by treatment group during the trial. They are independent and look at the trial from an ethical point of view of the participant safety, future patients and society in general. It is their responsibility to prevent patients being exposed to any excess risks by recommending to the Trial Steering Committee (TSC) for the trial suspension or termination early if the safety or efficacy results are sufficiently convincing. The trial statistician is usually invited to attend part of the DMEC meeting to present the most current data from the trial. This will be blinded, unless the DMEC specifically requests for an unblinded analysis.

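### Concealment is said to rest on all codes being off site, yet the protocol gives an on-site pharmacist, and without a stated need the trial statistician, access to the master code during the trial

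*Protocol*

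**What the plan says.** **Where the codes are.** Section 8.10.1.2 says caretakers, staff and investigators cannot know the next assignment, and gives one reason: "Because the master code and individual codes are kept in sealed envelopes in a central location off site". It refers the reader to section 8.10.2.

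**Who has access.** Section 8.10.2 says: "Only the study pharmacist (on site), and the trial statistician and the DMEC statistician (both off-site) will have access to master-code". This lasts until the study is completed or a stopping rule requires unblinding. The same section adds: "The randomisation scheme will also be available to the principal site investigator and the study safety monitor, but only as individual treatment code envelopes". Section 8.10.2.2 foresees that a master code may have been supplied to the pharmacy and must be returned to the sponsor.

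**When allocation is to become known.** Section 8.10.2 puts disclosure after data lock and after a SAP has gone to the DMEC. Section 8.10.2.2 has participants classified for the various analyses before the code is broken. Of the DMEC, section 16.3.3.2 says: "The members should be the only personnel to see the results separated by treatment group during the trial". That section also has the trial statistician present current data to the DMEC, blinded unless the DMEC asks for an unblinded analysis.

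**Who the statisticians are.** Section 8.10.1.1: "The randomisation schedule will be drawn-up in advance by the study statistician". Section 8.10.2: "The study statistician conducting the interim analysis will remain blinded throughout the analysis". Section 9.5.1.2 gives the interim analysis to an independent, blinded statistician.

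**What is still open.** Section 9.2 says the SAP supersedes the protocol and "will be drawn up during the course of the study before the unblinding of data at database lock". Section 9.2.3.3 leaves to it the major deviations that define the per-protocol population. Section 9.2.5.3 leaves to it the covariates and alternative models.

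**The concern.** There are two separate problems.

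The first is factual. The reason given for concealment does not agree with the section it cites. A reader checking how the next allocation was protected is pointed to text that describes something else.

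The second concerns the trial statistician. A pharmacist needs the code to pack, and a DMEC statistician needs it to serve the DMEC. No need is stated for the trial statistician, who also handles the accumulating data presented to the DMEC. Someone with both the code and the outcomes is able to compare the arms. If that person contributed to the SAP or to the analysis-set decisions, the protocol would give no way to show that those choices were made without knowledge of the treatment effect. At stake is how far the per-protocol, adjusted and sensitivity analyses can be shown to be independent of the results.

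**Working it through.** No arithmetic applies: the point depends on no rate, power or alpha. The check is a comparison of sections.

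1. **Location of the master code.** 8.10.1.2 places it centrally, off site. 8.10.2 lists an on-site pharmacist among those with access, and 8.10.2.2 allows for a copy at the pharmacy. These cannot all be literally true.

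2. **Location of the individual codes.** 8.10.1.2 places these off site too. 8.10.2 makes individual envelopes available to the site principal investigator. As worded, they give the treatment of subjects already randomised, so they contradict the stated location without in themselves revealing the next assignment.

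3. **What does protect the next assignment.** 8.10.1.2 describes opaque, sealed, identical-looking, sequentially numbered packs. 8.10.1.3 has the study ID written on the pack before opening, and the child counts as randomised from then. This is a sound mechanism and does not depend on where the code is kept. The defect is therefore in the stated reason; no failure of concealment is shown.

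4. **Trial statistician against the disclosure rule.** 8.10.2 grants access during the trial, and the same section defers disclosure until after lock and SAP submission. Both hold only if the trial statistician is an exception to the second rule, which the text does not say.

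5. **Trial statistician against DMEC-only results.** Access to a code is not the same as seeing results by arm. However, 16.3.3.2 provides for an unblinded analysis on DMEC request, in the context of the trial statistician's presentation. That is a foreseen route by which someone outside the DMEC would see such results.

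6. **Timing against open choices.** Access runs throughout the trial. The SAP is written within that period and fixes the per-protocol exclusions, covariates and alternative models. The protocol does not say who writes it or who classifies participants under 8.10.2.2.

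7. **Role names.** Four labels appear: study, trial, independent and DMEC statistician. The study statistician draws up the schedule (8.10.1.1), yet a study statistician conducting the interim analysis stays blinded (8.10.2). If the labels mean one person, these conflict. If they mean different people, they do not. The text does not settle which.

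**The case against.** The case on the other side is substantial, and much of it stands.

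- **Access is not possession.** The master code is described as sealed, and nothing says that the trial statistician opened it, linked it to outcomes or writes the SAP. A reader might infer that analysis choices were made unblinded. The protocol does not support that; it only fails to exclude it.
- **The primary analysis is not open.** Section 9.2.5.1 fixes intention to treat, all first and repeat events, the follow-up clock, Poisson regression stratified by country, and treatment as the only covariate.
- **The smaller sample size is not a symptom.** The target fell from 2212 to 1040, that is (2212 − 1040)/2212 = 53%, and a reader might connect this with code access. Section 8.8.1.1 calls the re-estimation blinded, made on DMEC and TSC recommendation from the pooled event rate and loss to follow-up. Neither needs the code. The changed inputs are stated openly in section 8.8.1: control rate 469 to 1,152 per 1000 child years, reduction 30% to 25%, power 90% to 80%, loss 15.7% to 10%.
- **The on-site roles are legitimate.** Someone must pack to the list. Sections 8.5.3.1 and 8.10.1.2 disclose that role as unblinded, and the latter bars that person from the rest of the study. The envelopes serve emergency unblinding, which 8.10.2.1 restricts and requires to be documented and reported.
- **The statistician labels may be loose wording only.** The blinded person in 8.10.2 can be read as the independent statistician of 9.5.1.2.

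What remains is the mismatch between 8.10.1.2 and 8.10.2, and an access grant to the trial statistician that has no stated purpose while a DMEC statistician already has access.

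**Conclusion.** The point holds as a contradiction over where the codes are kept and as an unexplained access right. The reason given for concealment in 8.10.1.2 is wrong as written, although the pack procedure can conceal allocation without it. The trial statistician's access fits poorly with deferred disclosure and with DMEC-only sight of results by arm. It leaves the blindness of the SAP's open choices unverifiable from the protocol.

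The size cannot be expressed as a bias. The exposure is limited to what is left to the SAP: the per-protocol definition, covariates and alternative models. It would extend to the primary analysis only if the superseding SAP changed section 9.2.5.1, and nothing indicates that. Nor do the documents support inferring that the code was used or that the sample-size change was informed by it.

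This rests on the protocol alone. The SAP is not at hand and may name its authors and state that they were blinded. The correction is worth making because it is cheap and removes a doubt that cannot easily be answered after unblinding.

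**What to change.** 1. In 8.10.2, from now until database lock and SAP sign-off, limit statistician access to the master code to the DMEC statistician.
2. State that the SAP authors, and those who classify participants into analysis sets under 8.10.2.2, remain blinded until then.
3. Record any access the trial statistician has already had, with dates and what was seen, including access through drawing up the schedule if that was the same person. The list was to be made in advance and enrolment began in May 2016, so appointing a new list-maker is no longer practical.
4. Correct 8.10.1.2 to say what is held on site (the packing pharmacist's list and the emergency code envelopes). Base concealment on the sealed, identical, sequentially numbered packs with the study ID written on the pack before opening.
5. Use one set of names for the study, trial, independent and DMEC statisticians in 8.10.1.1, 8.10.2, 9.5.1.2 and 16.3.3.2, and say who does what.

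The cost is an amendment of wording and a short access record. The one practical loss is that the trial statistician can no longer run unblinded analyses for the DMEC; the DMEC statistician, who already has access, would do them.

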#### 8.10.2.1. Emergency unblinding

The individual treatment code must not be broken by the investigator, except in medical emergencies necessitating the immediate identification of the treatment randomisation for the appropriate management of subject. The date, reason and name of person breaking the code must be documented and reported to the sponsor. If so clinically indicated, the subject will be withdrawn from receiving further study drug. Because the code is kept in individual envelopes, the treatment code can be maintained for the other subjects.

#### 8.10.2.2. Unblinding at the end of study

Before the treatment code is broken for statistical analysis, the code for each participant will be returned to the sponsor with a documented explanation for each episode where the code was broken. Any master code supplied (e.g. to the pharmacy) will be returned to the sponsor. No copies of the code will be taken by any of the investigators involved in the field work of the study. When the validation and editing process is concluded the formal 'locking' of the database will be documented. Data for each individual participant will be classified and coded with respect to its inclusion in the various statistical analyses planned in the study and the code entered into the data base. After the above actions have been documented the treatment code can be broken and included in the data base for each individual participant. Copies of the treatment code will be available to the investigator at the end of the study after the database is 'locked'.

## 9. DATA COLLECTION, MANAGEMENT AND ANALYSIS

### 9.1. DATA COLLECTION METHODS

Data will be collected and recorded at the point of contact; i.e. the health facility or at the study participants home by one of the trained study staff. Site supervisors will check data collection forms at the end of each day for completeness and accuracy of recording.

The study will use electronic care records forms to be entered using laptops, computer tablets and smartphones, and/or paper-based data collection forms and optical character recognition (OCR) software (e.g. HP TeleForm) for creating and scanning the forms. Completed clinical record forms and relevant source documents will be scanned on site or in a central location in each country and images will be transferred (encrypted) to a central server where they will be processed into databases via OCR.

#### 9.1.1. Data management

Original data collection forms will be handled only by study staff and kept under locked storage until completely coded, checked and transported for data entry. Once data entry and cleaning are complete any hard copies of CRFs will be stored for at least 3 years at secure storage facilities in Kenya and Uganda as per local storage policies and guidelines. After that CRFs will be shredded and copies of source data will be kept electronically in compliance with prevailing laws on data storage. If the study site is located in an area where KEMRI-CDC, Makerere University or other research groups are collecting demographic and health surveillance data will be linked using the unique identifiers for the individual or for the household of the individual to obtain household level demographic, educational and socio-economic data. After completion of the study, country specific data will be stored in each country, thus Kenyan data will be stored at KEMRI and the Ugandan specific data will be stored at Makerere University College of Health Sciences. The pooled data will be stored by the sponsor of the study, the Liverpool School of Tropical Medicine (LSTM), UK and the Norwegian Social Science Data Services (NSD, <http://www.nsd.uib.no/nsd/english/index.html>), as per requirements of the Research Council of Norway, who fund this trial. The electronic data will be kept for at least 15 years.

